##### Organizational parameter survey

The community partner champion(s) or administrator(s) will complete a Qualtrics XM® survey (Additional file 1) providing in-depth information about the organization’s characteristics including organizational partnerships, aggregate funding portfolio, workforce composition and training, staff-client or provider-patient ratios, annual number of end-users, characteristics of the geographic location, and internet and computer accessibility for both staff and end-users.

##### Process mapping

In collaboration with the community champion(s)/administrator(s), the academic partner will create a visual representation of the clinical workflow to get a clear understanding of the workflow processes in the organization. Iterative revisions and clarifications of the process map and a review by community partner leadership and frontline staff will identify any potential roadblocks, areas for improvement within the process, and determine an entry point(s) for the implementation of Gabby to ensure seamless integration into usual care. Process mapping will give insight to the client/patient care structure including individuals involved in the patient/client’s care plan, time allotted for each client/patient, types of services provided in conjunction with preconception care, types of internal and external-facing outreach and engagement activities, types of referrals (from and to whom), levels of case management intensity and location of case management (e.g. home, office visit), and the extent of other data collection and reporting done in the organization.

##### Organizational-level readiness assessment and identification of barriers and facilitators

Using a semi-structured interview guide (Additional file 2) grounded in the CFIR, a qualitative organizational readiness assessment to implement Gabby will be conducted with a diverse group of staff members representing frontline, administrative, and leadership staff at each community site. A quantitative scale based Qualtrics XM® survey (Additional file 3) will be used to concurrently assess organizational readiness and identify barriers and facilitators to implementation.

##### Site visit

The one-day site visit will serve as an opportunity for community and academic partners to interact in person before launching Gabby. The fun, interactive and collaborative site visit will allow for in-depth refinement of implementation activities including: a review of the process map, discussion of readiness assessment findings including how to address identified barriers, and a hands-on training of the Gabby System. At the conclusion of the site visit, key implementation decisions will be refined/finalized to identify persons directly involved in introducing Gabby and enrolling end-users, mechanics of when and how to engage end-users, and avenues for post-launch technical assistance.

##### Site visit follow up logistics call (~ 30 min)

A follow-up conversation will take place after the site visit with the community partner champion and any additional staff members that the champion elects to have on the call. The call will serve as an opportunity to address any concerns or barriers that arose during the site visit, review decisions made during the site visit and iron out details of the Gabby System launch, and make any final changes to recruitment material that will be mailed to the community partner by the academic partner. This discussion is particularly helpful in ensuring that the academic partner and community partner staff are on the same page in regard to implementation details and setting realistic expectations based on the site environment.

##### Launch webinar

A webinar hosted by the academic partner via the Zoom videoconferencing platform [35] will be conducted within 2 weeks of the anticipated start date of each site launching Gabby. During the webinar, the academic partner will review information covered during the site visit including the background and purpose, components of the Gabby System, frequently asked questions, and how to navigate the Gabby System from the end-user and administrator/staff perspectives. The webinar will provide an opportunity to review and clarify major decisions as well as address questions regarding client/patient recruitment and engagement that were discussed during the site visit and subsequent follow-up phone call. As the final step proceeding implementation and following the site visit, the launch webinar will be particularly geared towards frontline staff (e.g. community health workers, case managers) who will be introducing and/or enrolling end-users to ensure that they have the knowledge and tools to carry out implementation tasks.

##### Facilitate relay of clinical data to providers

Community partner staff will have access to the site-specific Gabby administrative page which will provide an overview of the health risks that end-users have identified as issues for concern and discussion. This clinical outcome data will inform providers and staff of health issues that need to be addressed with the client/patient in a follow up visit.

##### Technical assistance

For one month following the launch, the academic partner will provide technical assistance in the form of weekly calls with participating community partners. A semi-structured guide (Additional file 4) will be used to facilitate technical assistance calls and to capture a realistic sense of the progress of recruitment and implementation efforts. The calls will gauge any gaps in the pre-implementation process, resolve issues and identify resources to improve recruitment and engagement of staff and end-users. Technical assistance following the one-month requirement will occur as requested by the community partner. Community partners will also complete monthly implementation logs (Additional file 5) that capture reach (the proportion of Black and African American women willing to participate in the intervention), enrollment (the proportion of women who initiate engagement with Gabby), follow-up and referrals on flagged PCC-related risk factors (e.g. genetic health history, social and emotional well-being, healthcare access and affordability), and any technical issues that end-users and staff encountered. The primary purpose of the implementation log is to provide a quick snapshot of monthly implementation activities that inform reach, enrollment and the nature of interactions that frontline staff have with end-users about Gabby and/or PHHC topics discussed on a monthly basis.

#### Client/patient-facing implementation activities 

##### Engaging consumers: client/patient outreach and engagement

Community partner staff will use multiple means to recruit potential users including introducing Gabby during encounters in the client-staff or patient-provider visit, promoting Gabby at community outreach events, and disseminating Gabby information via the organization’s social media accounts (e.g. Facebook, Instagram, Twitter). Community partners will have an opportunity to follow Gabby on Facebook and Twitter for evidence-based health information and tips, links to health resources, videos, and podcasts specifically designed for Black and African American women, national Maternal and Child Health (MCH) awareness campaigns, and recognition of organizations, celebrities, and leaders who make positive contributions to Black and African American communities. This social media content is aligned with the health topics assessed by Gabby, and therefore will provide an opportunity for frontline staff to discuss health tips and topics that Gabby highlights with their clients or patients.

##### Allowance/incentive structures

A stipend of $1000 has been allotted for each community partner to be used to offset organization-specific challenges in outreach and enrollment efforts (i.e. monetary incentives, non-monetary incentives such as food or transportation vouchers, Gabby System compatible devices for use at the clinic or during home visits). In addition, the academic partner will provide Gabby branded materials including pens, cell phone wallets, tote bags, hand sanitizers, and earbuds to aid in outreach and recruitment efforts.

### Measures and data collection

This hybrid type II cohort study emphasizes both implementation and clinical effectiveness outcomes. We will use mixed methods in the form of individual interviews with staff and end-users, and a quantitative survey of staff to inform appropriateness, acceptability and feasibility outcomes. We conceptualize these mixed methods to be concurrent employing a consistent unit of analysis (staff and organization) across both forms of data, [36] such that qualitative interviews and quantitative survey measures will be collected separately from staff although analyses will complement each other in terms of overall study findings. Both quantitative and qualitative data will assess acceptability, appropriateness, and feasibility. Quantitative client/patient level Gabby System utilization data will be used to assess clinical effectiveness outcomes.

#### Qualitative data collection and measures

The academic partner (i.e. research staff) will engage key stakeholders from each site in virtual interviews prior to launching Gabby. We anticipate that 5–10 participants per site including frontline, administrative, and leadership staff will ensure that diverse perspectives and roles are represented, and will provide sufficient data for saturation, [37] although the exact number will be determined by community partner champions to reflect the organizational structure and workforce of the site. We will develop a semi-structured interview guide based on the CFIR domains (intervention characteristics, inner setting, outer setting, process, characteristics of individuals), select constructs within the domains, [30] and by adapting existing questions from the editable CFIR Interview Guide Tool [38]. Interview questions will examine perceptions of facilitators and challenges to implementing Gabby in community sites, the extent to which Gabby is congruent with the culture of each site, and organizational readiness.

The CFIR framework will also be used to guide identification of determinants of implementation, to select appropriate implementation strategies that match determinants identified, and to understand where those strategies can be employed in the implementation process. Strategy domains such as the action, action target, and implementation outcome affected will be outlined. This will ensure that the process for implementation is tailored to each site, directly informed by staff feedback, involves the engagement of site staff with different roles, and re-examines perceived barriers and facilitators over time. Data from this phase will be used to refine implementation strategies and inform appropriateness and acceptability implementation outcomes.

At the end of the implementation period leaders, clinicians, and administrative staff from each site who participated in the pre-launch phase will be invited to participate in an organizational stakeholder post-implementation virtual interview (Additional file 6). In the event of staff turnover, site champions will identify additional staff members to participate in a post-implementation interview. These data inform the feasibility implementation outcome, including staff perceptions of Gabby, the process of implementing the Gabby System within the community partner’s existing workflow and clinical context, and staff recommendations for scalability.

In collaboration with the community partner, the members of the academic research team will also conduct virtual interviews (Additional file 7) with end-users to evaluate perceptions of usability, usefulness, and cultural relevance of Gabby, and to gain a fuller understanding of the larger clinical context in which the implementation occurred.

With informed consent, all interviews with site staff and end-users will be conducted via the Zoom videoconferencing platform [35] and audio and video recorded. Audio recordings will be transcribed by a professional transcription service and reviewed by a research team member for accuracy. Web conferencing technology is an acceptable method of qualitative data collection especially among geographically dispersed participant populations, [39, 40] and the Zoom platform supports HIPAA compliance.

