ERIC Definition*	Identify and prepare individuals who dedicate themselves to supporting, marketing, and driving through an implementation	Assess various aspects of an organization to determine its degree of readiness to implement, barriers that may impede implementation, and strengths that can be used in the implementation effort	Distribute educational materials (including guidelines, fact sheets, flyers) in person, by mail, and/or electronically	Hold meetings targeted toward different stakeholder groups to teach them about the clinical innovation	Develop and use a centralized system to deliver technical assistance focused on implementation issues	Provide as close to real-time data as possible about key measures of process/outcomes using integrated modes/channels of communication in a way	Work to incentivize the adoption and implementation of the clinical innovation
Actor(s)	Academic partner staff; Community partner leadership, champion, frontline staff	Academic partner staff; Community partner leadership, champion, frontline staff, patients/clients	Academic partner staff; Community partner leadership, champion, frontline staff	Academic partner staff; Community partner leadership, champion, frontline staff	Academic partner staff; Community partner leadership, champion, frontline staff	Academic partner staff; Community partner leadership, champion, frontline staff	Academic partner staff; Community partner leadership, champion, frontline staff
Actions	Introduce Gabby System development history, purpose and duties of site champion, process map rationale. After completion of pre-implementation steps, readiness surveys will be distributed to staff	Organizational readiness and post implementation interviews with leadership, champion and frontline staff; Post implementation focus group with patients/clients	Access to educational and recruitment materials to distribute to staff and patients/clients	Review Gabby System mechanics, content areas, and site-specific implementation approach in an interactive format	Academic partner to address any technical issues identified by community partner in phone calls	Access to site-specific Gabby System administrative page	Monetary incentives, non-monetary incentives such as food or transportation vouchers, Gabby System compatible devices for use at the clinic or during home visits

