##### Introductory call (~ 30 minutes)

The primary purpose of this call will be to get buy-in and commitment from the community partner. The academic partner will provide background information about Gabby and convey the purpose and scope of the project to the community partner leadership or administrator(s). The academic partner will collect preliminary data on the organizational infrastructure and population served by the community partner. Community partner sites that commit to the implementation will be asked to identify a site champion who will serve as the primary point of contact to coordinate implementation activities.

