### Study status and special considerations

This study is now in the field and with modifications. As a result of the significant disruption that is being caused by the COVID-19 pandemic, the site visit pre-launch activity will be adapted to a virtual implementation facilitation session. Community partners will make adjustments to outreach and engagement efforts to virtual and other creative formats. Additionally, we anticipate community partners to grapple with changes in funding and staff turnover as a result of the pandemic. As such, community partners will be expanded to include community based primary care clinics as collaborators. Data collection for each community partner will include modifications and adaptations specific to the intervention and implementation before and after COVID-19. Analysis of implementation and clinical effectiveness outcomes will account for these time periods and changes across and within the organization.

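### Site champions, whose defined role is to promote Gabby, name the extra staff interviewed after turnover, so the staff-interview part of the feasibility evidence is open to favourable selection

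*Protocol article*

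**What the plan says.** Four parts of the Protocol article bear on this.

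- **Who the champion is.** Table 1, under Organization-facing implementation activities, gives the purpose of this strategy as "Identify and prepare individuals who dedicate themselves to supporting, marketing, and driving through an implementation". The Introductory call section asks each committed site to "identify a site champion who will serve as the primary point of contact to coordinate implementation activities". Table 1 also lists the champion among those interviewed before and after implementation.
- **Interviews before launch.** Qualitative data collection and measures plans 5 to 10 staff per site across several roles, "although the exact number will be determined by community partner champions to reflect the organizational structure and workforce of the site". Of this phase it says: "Data from this phase will be used to refine implementation strategies and inform appropriateness and acceptability implementation outcomes".
- **Interviews after implementation.** The same section re-invites staff who took part before launch, and adds: "In the event of staff turnover, site champions will identify additional staff members to participate in a post-implementation interview". These interviews are stated to inform feasibility, including staff views of Gabby, its fit with existing workflow, and recommendations for scaling up.
- **Turnover.** Study status and special considerations says "we anticipate community partners to grapple with changes in funding and staff turnover as a result of the pandemic". It gives no rate.

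**The concern.** The person whose job is to make the implementation succeed at a site names some of the people who will say whether it succeeded. The stated procedure does not require a replacement to hold the same kind of post as the leaver or to have used or introduced Gabby. Nor does it require agreement from the academic partner. Champions may well choose colleagues who were engaged and supportive, without intending any distortion, and those colleagues may report fewer obstacles than others in the same role.

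Appropriateness, acceptability and feasibility form one of the two co-primary aims, and the study promises a toolkit built on the barriers and facilitators it finds. If the later staff interviews lean towards supporters, the feasibility account may look better than it should, and the toolkit may miss workflow problems that another site will meet.

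**Working it through.** The article states no figure for this point, so there is none to reproduce. The check is a reading of the rules together, followed by a simple count.

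**Step 1. Where the champion has a say over staff interviews**

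- *Number interviewed before launch:* set by the champion. The stated purpose of that phase is to refine strategies and inform appropriateness and acceptability. Feasibility is not named.
- *Individuals interviewed before launch:* the article does not say who picks them.
- *Individuals re-invited afterwards:* fixed by rule, namely those who took part before launch.
- *Additional individuals after turnover:* named by the champion, with no criterion stated. These interviews inform feasibility.

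Only in the last case does the text give the champion a choice of individuals. Control of the number reaches feasibility only indirectly, because the pre-launch participants form the later invitation list.

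**Step 2. Whether other feasibility evidence shares the weakness**

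- Quantitative analysis also assesses feasibility from uptake and usage, that is, logins and minutes per end-user. These come from the system and no one selects respondents.
- End-user interviews are conducted by the academic team in collaboration with the community partner. The champion is not stated to choose who takes part.
- Technical assistance calls and monthly implementation logs record technical issues and recruitment progress. They are reported by the community partner, so they are a separate source but not a fully independent one.

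None of these is a staff account of workflow given after implementation by someone chosen independently of the site. They limit the damage but do not replace the interviews.

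**Step 3. How many interviewees could be affected**

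Inputs: 12 sites (Aims and objectives) and 5 to 10 staff per site (Qualitative data collection and measures). The turnover share *t* is an assumption. So are one-for-one replacement and acceptance by all remaining staff.

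- Staff interviewed before launch: 12 × 5 = 60 to 12 × 10 = 120.
- Champion-named interviewees = 12 × (5 to 10) × *t*:
  - *t* = 10%: 6 to 12
  - *t* = 30%: 18 to 36
  - *t* = 50%: 30 to 60
- At *t* = 30%, that is 1.5 to 3 people per site.

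Under these assumptions the champion-named share of post-implementation interviews equals *t* itself. The count shows how many interviews are exposed. It does not measure bias.

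**The case against.** The strongest reply is that the rule is narrow and the safeguards are real. Staff who remain are re-invited without any choice by the champion. The pre-launch number must reflect the site's structure and workforce, and frontline, administrative and leadership roles are expected. Feasibility also draws on login data, end-user interviews, logs and calls. These are key informant interviews, where purposive choice by someone who knows the site is normal, and nothing shows that a replacement would be more favourable than the person replaced. Finally, an article condenses a fuller protocol that may say more.

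Most of this stands and sets the limits of the point. It rules out several stronger readings that a reader might infer:

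- *That all feasibility evidence is filtered by the champion.* Uptake, usage and end-user interviews are not stated to pass through that person.
- *That the champion hand-picks the pre-launch interviewees.* The text gives control of the number only.
- *That staff who leave are shut out.* The article speaks of additional interviewees and does not say leavers are excluded. Their loss is plausible but inferred.
- *That the readiness survey fails as a check on who was chosen.* Quantitative data collection and measures pairs it with the pre-launch interview to compare the same staff's answers. It was not designed to test selection, and it precedes any replacement.

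The argument from condensation does not dispose of the rest. The article states a positive rule about who names the additional interviewees, so the point does not rest on a missing detail. Purposive sampling is acceptable, but the choice need not lie with the person charged with promoting the intervention.

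**Conclusion.** The point holds in a limited form. The article lets a person with a defined promotional role name the additional staff interviewed after turnover. It states no role-matching and no independent check, and it expects turnover. The staff-interview component of the feasibility evidence is therefore open to favourable selection. The direction is a reasonable inference from the champion's role and is not a demonstrated effect.

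The size cannot be determined from the document. With assumed turnover of 10% to 50% and one-for-one replacement, between 6 and 60 interviewees would be champion-named, and most of that spread comes from the assumption. This is a credibility weakness in one component of a co-primary aim that can be repaired cheaply. It does not undermine the feasibility assessment as a whole.

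**What to change.** In Qualitative data collection and measures, replace the turnover sentence with a rule of this kind: each site supplies a list of staff who have been trained on Gabby or introduce it to end-users; where an earlier interviewee has left, the academic partner chooses and invites a replacement from that list, matched to the leaver's role. The champion can still supply the list and help with scheduling.

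Also identify the champion's own interview in the analysis, so that the feasibility findings can be read with and without it. Transcripts are to be de-identified but carry site numbers, so this label could point to one person at a site. It is best kept within the research team and used in results pooled over sites.

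The cost is one staff list per site and slightly more coordination over invitations. The interview guides stay as they are. The study is already in the field, but the change can apply to every post-implementation interview not yet held.
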